In patients undergoing endovascular treatment for aSAH, continuous maintenance of arterial catheters with UFH during surgery contributes to the reduction of thrombus formation, while subcutaneous injections of low-molecular-weight heparin (LMWH) prevent formation of lower-extremity deep veinous thrombosis. However, both LMWH and UFH infusions have their pros and cons. Although neurocritical care guidelines recommend initiating subcutaneous heparin 24 h after aneurysm embolization surgery [9], the UFH injection has limitations due to its high molecular weight and low bioavailability. Intravenous UFH may, therefore, be considered more reliable.

Research indicates that low-dose intravenous UFH infusion yields favorable outcomes in reducing CV and ischemic complications. Multiple retrospective studies have demonstrated the safety and efficacy of low-dose continuous intravenous UFH infusion. However, there is controversy regarding the optimal dosage and duration of treatment. A retrospective study by J. Marc Simard revealed the safety of low-dose (8–9 U/kg/h) intravenous UFH administration in aSAH patients, without any cases of bleeding, heparin-induced thrombocytopenia (HIT), or deep vein thrombosis, and the incidence of clinical vasospasm significantly decreased compared to subcutaneous LMWH usage [10]. Another research by Markus Bruder in endovascular treatment for aSAH patients showed a lower probability of cerebral infarction when combining UFH with LMWH [11].

Regarding the timing of initiating of heparin, Annika’s study suggested that using heparin within 24 h after aneurysm repair might be safer and carry a lower risk of bleeding compared to initiating treatment 48 h later [12]. Randomized controlled trial results comparing subcutaneous injections of LMWH and intravenous infusion of UFH are currently lacking, although randomized controlled studies have shown the safe and effective reduction of CV and ischemia with subcutaneous injection of enoxaparin compared to placebo in patients with aSAH [13].

This study is a single-center exploratory randomized controlled trial comparing the impact of low-dose intravenous infusion of UFH and subcutaneous injection of LMWH on the incidence of CV in aSAH patients. The outcomes to be assessed also include the occurrence of bleeding events, ischemic events, HIT, deep vein thrombosis, cerebral venous circulation time, brain edema score, and hydrocephalus incidence.

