### Primary and secondary outcomes

The primary outcome was the incidence of CV, while secondary outcomes included the incidence of bleeding events, ischemic events, HIT, deep vein thrombosis, cerebral venous circulation time, brain edema score, and incidence of hydrocephalus. The time points for the primary outcomes are the first and second weeks following the patient’s hospitalization and intervention treatment. The time points.for the secondary outcomes include the first 3 days after hospitalization, the first and second weeks, and the follow-up within 1 year after discharge. The CV was defined as the presence of significant neurological deficits in patients, with TCD ultrasound assess a mean flow velocity of the middle cerebral artery (MCA) exceeding 120 cm/s or a Lindegaard ratio (mean flow velocity of MCA/mean flow velocity of extracranial internal carotid artery) greater than 6. Computed tomography angiography scans showed temporary narrowing of cerebral artery. Regardless of the severity or clinical status of the patient, it was evaluated as CV.

Bleeding events are defined as bleeding that occurs in any part of the body, including intracerebral hemorrhage, gastrointestinal bleeding, and subcutaneous bleeding. According to the standardized bleeding score of Bleeding Academic Research Consortium (BARC), it has 5 types [18]. Type 1 refers to bleeding that is considered insignificant and does not prompt the patient to seek medical attention. Type 2 bleeding includes any obvious sign of hemorrhage that requires medical attention, diagnostic testing, hospitalization, or treatment by a healthcare professional. Type 3 bleeding encompasses clinical, laboratory, and/or imaging evidence of bleeding that requires a specific response from a healthcare provider. Type 4 bleeding is related to coronary artery bypass grafting within 48 h, and type 5 bleeding is fatal. Fatal bleeding can be categorized as intracranial, gastrointestinal, retroperitoneal, pulmonary, pericardial, genitourinary, or other.

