Ischemic events include cerebral and cardiac ischemia, with cerebral ischemia encompassing transient ischemic attacks and stroke, while cardiac ischemia includes angina pectoris and myocardial infarction. HIT is defined as a decrease in platelet count of 50% or more after the therapy of heparin. Deep venous thrombosis includes lower limb deep venous thrombosis and pulmonary embolism, which is diagnosed by a respiratory physician based on pulmonary vascular examination and blood D-dimer testing. The diagnose of lower limb deep venous thrombosis is detected by ultrasound. Hydrocephalus is defined as an enlargement of the cerebral ventricles as visualized on a brain CT scan.

Cerebral venous circulation time is defined as the time required for blood to enter the venous sinus through the deep and superficial veins of the brain and then be drained into the jugular vein, including microvascular cerebral circulation time, venous cerebral circulation time, and the PRECISE score. Following S. Wang’s research, the starting point T1 is set as the first image in the sagittal view of digital subtraction angiography (DSA), which depicts the contrast dye within the branches of the middle cerebral cortical arteries [19]. The vein image that shows the peak filling of the parietal cortical vein is set as T2, and the only disappearance of the sigmoid sinus was set as T3. The mCCT is expressed as T2-T1, while vCCT is expressed as T3-T2.

The PRECISE score is based on the venous filling level shown on the head CTA. A score of 2 represents complete filling that is consistent with the degree of filling in the contralateral hemisphere, while a score of 1 represents partial filling, and a score of 0 indicates no filling. The filling difference of the affected hemisphere veins is calculated based on the PRECISE score. A higher score indicates the improved cerebral venous outflow, while a lower score signifies the decreased cerebral venous outflow. A score of 2 will be given for “complete” contrast filling of the opposite hemisphere, while a score of 1 will be given for “partial” (moderate contrast filling). The PRECISE score will be calculated using the composite score of the normal hemisphere SMCV + VOT + VOL + BVR minus the composite score of the lesioned hemisphere SMCV + VOT + VOL + BVR [20].

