### Statistical analyses

The data analysis will be carried out with statistical software (SPSS, version 26, SPSS Inc). The covariates between groups will be balanced based on Propensity score matching (PSM). The results of outcomes will be analyzed for differences between the UFH group and LMWH group, using the Student *t*-test, chi-square test, and Mann–Whitney *U* test. For continuous variables, the normality test is estimated using the mean (standard deviation). If parameters are not normally distributed, their median (interquartile range) will be reported. For categorical variables, the proportions of the two groups will be presented. Spearman’s correlation analysis is performed on nonnormal continuous variables. Pearson’s correlation is employed for categorical variables. Variables with differences between the two groups will be analyzed by univariate analysis and multifactor logistic regression. Cox multivariate regression analysis will be used for time-to-events data. All statistical tests are two-sided with *p* < 0.05, crude odds ratio (OR), and confidence intervals (CI) will be calculated. In addition, the number of recruitments, participants lost due to follow-up, violations of the protocols, and other relevant descriptive data will be reported. The missing data will be handled using multiple imputation methodology.

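### If heparin-induced thrombocytopenia or deep vein thrombosis proves rare, the named crude odds ratio can fail and leave no bound on harm; a risk difference with a score or exact interval avoids this at little cost

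*Protocol article*

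**What the plan says.** The Statistical analyses section of the protocol article treats all outcomes together: "The results of outcomes will be analyzed for differences between the UFH group and LMWH group", by the t-test, "chi-square test, and Mann–Whitney" U test. Of these three, chi-square is the one for a binary outcome. The effect measure follows in the same paragraph: "crude odds ratio (OR), and confidence intervals (CI) will be calculated". The method for the interval is not named. The section also states: "For categorical variables, the proportions of the two groups will be presented". Logistic regression is mentioned for variables that differ between the groups, and Cox regression for time-to-event data.

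The binary secondary outcomes are defined under Primary and secondary outcomes:
- HIT: "HIT is defined as a decrease in platelet count of 50% or more after the therapy of heparin".
- Deep vein thrombosis, which by definition includes pulmonary embolism.
- Bleeding, defined broadly: "Bleeding events are defined as bleeding that occurs in any part of the body". It is graded by BARC type, and "type 5 bleeding is fatal" is one grade within that outcome.

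The Background describes the cited retrospective cohort on low-dose intravenous unfractionated heparin as "without any cases of bleeding, heparin-induced thrombocytopenia (HIT), or deep vein thrombosis". It does not give the size of that cohort.

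**The concern.** The one piece of evidence in the document on the frequency of HIT and deep vein thrombosis under low-dose intravenous heparin is a count of zero. An odds ratio is a poor effect measure when zero is a plausible count. With one empty arm it is 0 or infinite, and the usual Wald interval needs the reciprocal of a zero cell. With no events in either arm, both chi-square and the odds ratio are undefined.

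The abstract says that continuous intravenous heparin is debated because of bleeding risk, and the Discussion gives safety as an aim of the trial. For a rare harm, the useful result is how large the excess risk could still be. The named effect measure may not supply it.

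**Working it through.** **Inputs.** 228 patients per arm and 10% dropout (Sample size estimation), so 228 × 0.9 ≈ 205 evaluable per arm. The Randomization and blinding section gives 143 per arm instead; that conflict is a separate matter, and the figure is carried here as a lower case. The document states no event rate for HIT or deep vein thrombosis, so there is no planned figure to reproduce. The rates below are assumptions, taken as equal in both arms.

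**Chance of an empty arm.** With rate p and n per arm, P(at least one arm without events) = 1 − [1 − (1 − p)^n]². For p = 1% and n = 205: 0.99^205 = 0.127, and 1 − 0.873² = 0.24.

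| Assumed rate | Expected events per arm (n = 205) | n = 228 | n = 205 | n = 143 |
|---|---|---|---|---|
| 0.2% | 0.41 | 87% | 89% | 94% |
| 0.5% | 1.02 | 54% | 59% | 74% |
| 1% | 2.05 | 19% | 24% | 42% |
| 2% | 4.10 | 2.0% | 3.2% | 10.8% |
| 3% | 6.15 | 0.2% | 0.4% | 2.6% |

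The problem is therefore real at about 1% or less and largely gone by 2% to 3%. Expected counts fall below 5 when the mean rate is under 5/205 = 2.4% (5/228 = 2.2%).

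**What each method gives for 4 v 0 events, 205 per arm.**
- Crude odds ratio: (4 × 205)/(0 × 201), infinite. The Wald standard error contains 1/0, so there is no interval.
- Odds ratio with 0.5 added to each cell: (4.5 × 205.5)/(0.5 × 201.5) = 9.2, 95% interval 0.49 to 172.
- Conditional exact interval for the odds ratio: 0.66 to infinity. With the arms exchanged it is 0 to 1/0.66 = 1.5, so this interval is finite on one side only.
- Risk difference: 4/205 − 0/205 = 2.0%, Newcombe score interval −0.2% to 4.9%. It is finite on both sides.
- Uncorrected chi-square: 410 × (4 × 205)² / (205 × 205 × 4 × 406) = 4.04, p = 0.044. Fisher: 2 × C(205,4)/C(410,4), p = 0.12.

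**Bound for an empty arm.** For 0 of 205, the two-sided 95% Clopper-Pearson upper limit is 1 − 0.025^(1/205) = 1.8%. For 0 of 228 it is 1.6%.

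**Type I error of uncorrected chi-square**, by enumeration at a nominal 5% with 205 per arm: 0.1% at a rate of 0.2%, 1.5% at 0.5%, 4.1% at 1%, 4.5% at 2% and 4.8% at 5%. It never exceeds 5% over these rates. A single sparse table can still cross 0.05 under one test and not under another, as above.

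**The case against.** The strongest reply is that this is one paragraph of a journal article. A rule for sparse tables, an interval method and a minimum number of events are details that the full protocol or analysis plan would normally hold, and neither is shown. That stands as a limit on severity. It does not remove the point, because the article does name a test and an effect measure for outcomes in general, and the effect measure fits these outcomes poorly.

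The second reply is that rarity is assumed. No events in one retrospective cohort of unstated size does not establish a rate, and the definitions here are fairly broad. This also stands, and the conclusion is conditional for that reason.

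A reader might infer more than the document supports:
- That no usable estimate would remain. Group proportions will be presented and can carry exact limits, and no Wald interval is prescribed.
- That fatal bleeding or pulmonary embolism is compared on its own. The first is a grade within a broad bleeding outcome that need not be rare; the second is counted within deep vein thrombosis.
- That every rare outcome goes on to a logistic or Cox model. The text assigns logistic regression to variables that differ between groups, and does not say whether these include outcomes.
- That equal safety would be concluded from p > 0.05. The plan says nothing of the kind.

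**Conclusion.** The point holds in a limited form. Chi-square and a crude odds ratio are the comparison named for binary secondary outcomes, HIT and deep vein thrombosis included. If their rates are about 1% or less, an arm without events is fairly likely (24% at 1% and 59% at 0.5% with 205 per arm). The odds ratio is then 0 or infinite, its usual Wald interval does not exist, and the named measure gives no bound on harm. At 2% the chance is only about 3%, and little is at stake.

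This rests on assumed rates, equal in both arms, and on 205 evaluable per arm. Smaller arms, through the conflicting total of 286 or through the planned propensity score matching, would make empty arms more likely. It would be tempting to read the p = 0.044 example as a sign of excess false positives. The enumeration does not support that: the type I error stays below 5%. The size of the point is that of a minor improvement to secondary analyses.

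**What to change.** In the Statistical analyses section, or in the analysis plan before any data are compared, add a rule for HIT, deep vein thrombosis and any bleeding grade that turns out sparse:

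1. Report events and denominators by arm, and use the risk difference with a score or exact 95% confidence interval as the effect measure.
2. Use an exact test such as Fisher's when any expected count is below 5.
3. Do not fit an ordinary logistic or Cox model for the treatment effect when an arm has no events.

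The cost is a few lines of analysis wording. No data collection, sample size or clinical procedure changes. Depending on the interval method chosen, software other than the named package may be needed.

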### Outcome assessments

#### Baseline assessment

Baseline variables encompass demographic information (gender, age, ethnicity, prior medical history, personal life history), comorbidities, vital signs (blood pressure, heart rate, respiratory rate), concomitant medication, surgical intervention (e.g., decompressive craniectomy), and results of the laboratory tests. In addition, Hunt-Hess scales [14] and World Federation of Neurosurgery Societies (WFNS) [15] grade were used to assess the severity of clinical symptoms. Modified Fisher score [16] was employed to evaluate the degree of CV. Assessment of functional independence was performed by the Modified Rankin Scale (mRS) [17]. All clinical baseline data were conducted upon admission and during hospitalization by two researchers who were unaware of the group assignment.

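### Pearson's correlation is assigned to categorical variables without limit; for unordered variables with three or more levels its result depends on arbitrary numbering (minor, secondary analysis only)

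*Protocol article*

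**What the plan says.** The Statistical analyses section of the protocol article assigns correlation methods in two consecutive sentences. The first reads "Spearman’s correlation analysis is performed on nonnormal continuous variables" and the second "Pearson’s correlation is employed for categorical variables". Normally distributed continuous variables are given no correlation method. The second sentence sets no limit on the kind of categorical variable and names no coding.

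Differences between the UFH and LMWH groups are handled separately, "using the Student *t*-test, chi-square test, and Mann–Whitney *U* test". The significance rule is general: "All statistical tests are two-sided with *p* < 0.05".

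The article does not say which variables will be correlated with which. It also does not say that the correlation results select variables for the regression models; entry there is tied to differences between the two groups.

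Some of the information collected can be unordered with several levels. The Baseline assessment section lists "demographic information (gender, age, ethnicity, prior medical history, personal life history", among other items.

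**The concern.** Pearson's r measures linear trend across numeric scores. Its null hypothesis is that there is no linear trend in those scores. A nominal variable with three or more levels has no natural scores, so an analyst must invent them, and a different numbering of the same categories can change the size, sign and p-value of r. A real association can then appear as no correlation, or a correlation can be reported that relabelling would reverse.

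The two sentences look like a misplaced assignment. The usual counterpart to Spearman for non-normal continuous variables is Pearson for normal ones, and that is the class left without a method. What is at stake is whether any coefficients reported for nominal variables can be interpreted.

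**Working it through.** The plan states no figure on this point, so there is none to reproduce. The check asks whether r really depends on coding, and for which kinds of variable.

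**Inputs.** Total N = 456 is from the Sample size estimation section. (The Randomization and blinding section gives 286. The choice does not matter here, because at fixed proportions r does not depend on N.) The same Sample size section cites vasospasm (CV) rates of 58% and 60%. Assumptions made here: a three-level nominal variable with 152 patients per level, and CV rates around those figures.

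**Case 1: rates of about 50%, 70%, 50%.** CV counts are 76, 106, 76, in total 258 with CV and 198 without. With no association, each level expects 86 with CV and 66 without, so the deviations in CV counts are −10, +20, −10.

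- Chi-square = (100 + 400 + 100)/86 + (100 + 400 + 100)/66 = 6.98 + 9.09 = 16.07 on 2 df, p = 0.0003. No codes enter the formula.
- Pearson: r = Sxy / √(Sxx · Syy), with Sxx = 152 × (1 + 0 + 1) = 304 and Syy = 258 × 198/456 = 112.03, so the denominator is 184.5.
- Codes 1, 2, 3: Sxy = (−1)(−10) + (0)(20) + (1)(−10) = 0, so r = 0.00, p = 1.00.
- Codes 1, 3, 2: Sxy = (−1)(−10) + (1)(20) + (0)(−10) = 30, so r = 30/184.5 = 0.163, p = 0.0005.
- Codes 2, 1, 3: Sxy = (0)(−10) + (−1)(20) + (1)(−10) = −30, so r = −0.163, p = 0.0005.

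Identical data therefore give a zero, a positive or a negative correlation.

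**Case 2: rates of about 50%, 70%, 54%.** CV counts are 76, 106, 82, in total 264; the deviations from 88 are −12, +18, −6.

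- Chi-square = 504/88 + 504/64 = 5.73 + 7.88 = 13.60, p = 0.001.
- Syy = 264 × 192/456 = 111.16, so the denominator is 183.8.
- Codes 1, 2, 3: r = 6/183.8 = 0.033, p = 0.49.
- Codes 2, 1, 3: r = −24/183.8 = −0.131, p = 0.005.
- Codes 1, 3, 2: r = 30/183.8 = 0.163, p = 0.0005.

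**Simulated rejection rates.** In 5,000 trials with N = 456 and true rates 50/70/50%, the chi-square test rejects in 97%. Pearson rejects in 5% under codes 1, 2, 3 (no more than alpha) and in 95% under codes 1, 3, 2.

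**Binary check.** For two binary variables, N·r² equals the uncorrected chi-square. In a 2×2 example with N = 456 and r = ±0.1014, N·r² = 456 × 0.01028 = 4.69, equal to the chi-square of 4.69, with p = 0.030 for both. Recoding changes only the sign. There is no harm in this case.

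**Ordinal scores.** For Hunt-Hess, WFNS, modified Fisher, mRS and SEBES the order fixes the direction. Pearson's r is then a trend test that assumes equal spacing, which is a matter of preference and not an error.

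**The case against.** The strongest reply is that little in this trial depends on the sentence. CV, bleeding events, ischemic events, HIT, deep vein thrombosis and hydrocephalus are analysed as incidences, so they are yes/no per patient and r is phi. Categorical outcomes have the chi-square test for the comparison between arms. No correlation of a multi-level nominal variable is announced. All of this stands.

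Several possible examples are also weak:

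- Ischemic event type. The text "Ischemic events include cerebral and cardiac ischemia, with cerebral ischemia encompassing transient ischemic attacks and stroke, while cardiac ischemia includes angina pectoris and myocardial infarction" lists what counts as an event. It does not define a four-level analysis variable, and one patient may have more than one kind.
- BARC type. A reader might call it unordered because "Type 4 bleeding is related to coronary artery bypass grafting within 48 h, and type 5 bleeding is fatal". In patients enrolled for endovascular aneurysm treatment, type 4 should be almost empty, and types 1, 2, 3 and 5 run in order of severity.
- Site of fatal bleeding. "Fatal bleeding can be categorized as intracranial, gastrointestinal, retroperitoneal, pulmonary, pericardial, genitourinary, or other" does give seven unordered categories, but only for fatal bleeds, and no analysis of site is described.
- Ethnicity. The Strengths and limitation section describes an exclusively Asian population, so three populated levels cannot be assumed.

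A reader might infer from the simulation that the trial stands to lose some 90 percentage points of power. The documents do not support that. The 50/70/50% pattern under codes 1, 2, 3 makes the linear trend zero by construction, and under another coding the loss is about 2 points (95% against 97%).

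Finally, the sentence may be a slip, either for Pearson's chi-square or for Pearson's correlation on normal continuous variables. The separate listing of chi-square does not rule out the first reading, since that listing concerns differences between arms. But the text says correlation and sets it beside Spearman's, and nothing in the article corrects it. A probable slip is a reason to reword it.

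**Conclusion.** The assignment is wrong as written for any nominal variable with three or more levels, for example ethnicity or medical-history categories if they are so coded. There, r and its p-value can run from nothing to p = 0.0005 on the same data, according to the numbering. The gap for normally distributed continuous variables belongs to the same error.

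This is a minor error in a secondary analysis. A reader might infer that it endangers the primary comparison, or makes every reported correlation uninterpretable. The documents support neither: the comparisons between arms use other tests, binary variables are unaffected, and ordinal scores still give a meaningful trend.

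The existence of the coding dependence needs no assumption about the trial. Its size here rests on assumed equal levels and chosen non-monotone CV rates, and it is an illustration, not an estimate of harm. Whether it will arise at all depends on which variables are correlated, which the article does not say.

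**What to change.** Replace the two correlation sentences in the Statistical analyses section with:

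*Pearson's correlation will be used for normally distributed continuous variables, Spearman's for non-normal continuous and ordinal variables, and association between nominal variables will be tested by chi-square or Fisher's exact test and summarised with Cramér's V.*

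The cost is one sentence of text. It needs no new data, patients or procedures, and the methods are standard. It should be settled before the analysis, so that no choice of coding is left open once the data are seen.

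### No covariate-adjusted analysis of CV is prespecified, so the severity scores already collected are not reliably used and precision is lost

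*Protocol article*

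**What the plan says.** All references are to the protocol article.

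- **Outcome.** Under Primary and secondary outcomes: "The primary outcome was the incidence of CV". Each patient either has CV or does not.
- **Outcome tests.** Under Statistical analyses: "The results of outcomes will be analyzed for differences between the UFH group and LMWH group", by t-test, chi-square test or Mann–Whitney U test. Only chi-square suits a binary endpoint. On the significance level and effect measure it says: "All statistical tests are two-sided with *p* < 0.05, crude odds ratio (OR), and confidence intervals (CI) will be calculated".
- **Covariates.** The same section says "The covariates between groups will be balanced based on Propensity score matching (PSM"), without listing those covariates. It then sends variables that differ between the arms to univariate analysis and multifactor logistic regression. It does not say which of these analyses gives the main result for CV.
- **Scores collected.** Under Baseline assessment: "Hunt-Hess scales [14] and World Federation of Neurosurgery Societies (WFNS) [15] grade were used to assess the severity of clinical symptoms", and "Modified Fisher score [16] was employed to evaluate the degree of CV". Age is recorded too. That section places the collection of baseline data both at admission and during the hospital stay.
- **Allocation.** Randomization and blinding describes a shuffled list of IDs cut into two fixed halves. No stratification by severity is described.

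**The concern.** A baseline score that predicts CV explains part of the variation in the outcome. A chi-square test leaves that part in the error term, whereas a model fixed in advance to include the score removes it at no cost in patients. The trial collects three such severity measures, and nothing written guarantees that any of them enters the analysis of CV.

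The two covariate steps that are planned do not close the gap. Matching is on unnamed covariates, so modified Fisher and WFNS may or may not be among them. The regression admits a variable because the arms happen to differ on it. A strongly prognostic score that happens to be balanced stays out, and its precision gain is lost. Letting the observed difference choose the covariates also leaves the reported model undetermined until the data are seen.

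At stake are some power in a trial that has little to spare and a clear statement of which odds ratio is the main result.

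**Working it through.** **Inputs from the protocol article.** Sample size estimation: 228 per arm, 10% dropout, two-sided α = 0.05, target effect 0.1 (scale not stated), cited CV rates 58% (UFH) and 60% (LMWH). Power is not stated.

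**Assumptions.** The target of 0.1 is read as 60% v 50%. Prognostic strength is given nowhere, so a range is shown. Evaluable per arm: 228 × 0.9 = 205.2, taken as 205.

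**1. The plan's own figure.** Two-sided superiority at 60% v 50% with 80% power (assumed), pooled variance under the null:

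n = [1.96 × √(2 × 0.55 × 0.45) + 0.842 × √(0.24 + 0.25)]² / 0.1² ≈ 388 per arm, and 388 / 0.9 ≈ 432 with dropout.

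The stated 228 is not reproduced. That is a separate matter, but it explains why the baseline power below is low.

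**2. Unadjusted power.** SE = √[(0.60 × 0.40 + 0.50 × 0.50) / 205] = 0.0489. Then 0.1 / 0.0489 = 2.045, and power = Φ(2.045 − 1.96) = 0.534. The pooled-variance version gives 0.530. Both are about 53%.

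**3. Adjusted power, approximation.** With correlation ρ between score and outcome, the variance is multiplied by 1 − ρ²:

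| ρ (assumed) | 2.045 / √(1 − ρ²) | Power | Gain |
|---|---|---|---|
| 0.3 | 2.144 | 57.3% | 4 points |
| 0.4 | 2.232 | 60.7% | 7 points |
| 0.5 | 2.362 | 65.6% | 12 points |

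With 143 per arm, the other size the article states, power goes from 40.1% to 50.5% at ρ = 0.5.

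**4. Adjusted power, simulated logistic regression.** 205 per arm, 60% v 50%:

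| Score | Unadjusted | Adjusted |
|---|---|---|
| Four-level, ρ = 0.3 | 53.5% | 56.0% |
| Four-level, ρ = 0.4 | 53.8% | 59.9% |
| Four-level, ρ = 0.5 | 51.9% | 63.1% |
| Continuous, AUC 0.64 | 53% | 55% |
| Continuous, AUC 0.74 | 54% | 62% |
| Continuous, AUC 0.81 | 55% | 68% |

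The gain runs from about 2 to 13 points. A score with no prognostic value gains nothing (54% v 53%).

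**5. Does the planned regression recover the gain?** The rule is read here as adjusting only when the score differs between arms at p < 0.05, which happens in about 5% of trials. Power in 4,000 simulated trials per row:

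| Log-OR per SD | Crude | Article's rule | Always adjusted |
|---|---|---|---|
| 0.5 | 55.5% | 55.8% | 56.2% |
| 1.0 | 53.8% | 53.9% | 60.8% |
| 1.5 | 53.3% | 53.7% | 66.4% |

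The rule recovers almost none of it. The first row also shows that a weak score gains very little, within simulation error.

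**6. Validity.** With 60% in both arms, the unadjusted test rejects in 4.4–4.9% of trials in one set of runs and 4.6–5.4% in another. Overall type I error is intact.

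**7. At the cited rates (60% v 58%).** SE = √[(0.60 × 0.40 + 0.58 × 0.42) / 205] = 0.0486; 0.02 / 0.0486 = 0.412; Φ(0.412 − 1.96) ≈ 6%. At ρ = 0.5 it is Φ(0.412 / 0.866 − 1.96) ≈ 7%, a gain of under 1 point.

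**8. Matching.** If matching discards 5%, 10% or 15% of pairs (assumed), unadjusted power at 60% v 50% falls to 51%, 49% or 47%.

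**The case against.** **Adjustment is planned.** A reader might infer from the crude odds ratio that neither design nor analysis deals with baseline severity. The article does not support that: matching and multivariable regression are both in the same section. If the tests are run after matching on these scores, the crude odds ratio comes from a balanced sample. This stands. What remains is that the matching covariates are unnamed and the regression rule is driven by the data, so use of the scores is not assured.

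**The unadjusted test is valid.** A reader might also infer that chance imbalance undermines the result. It does not: the p-value already allows for it, and step 6 shows error near 5%. In the roughly 1 trial in 20 where the score is significantly imbalanced, the crude test rejects a true null more often (8% to 21% across the strengths simulated, on few trials each). That supports adjusting, but does not show that the test is wrong.

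**No analysis is designated primary.** That chi-square is the primary test is an inference from the outcome type. This stands, and is part of the defect.

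**Covariates are commonly left to the SAP.** That is true, and silence would be no finding. But the article positively promises a crude measure and states a rule for choosing regression variables. If a SAP already fixes an adjusted model, only the article's wording needs aligning.

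**The size is assumed.** This stands. No prognostic strength is given; the upper end needs a strong score (AUC about 0.8), and the figures use unmatched patients.

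**The scores may not all be baseline values.** This stands too. Some data are recorded during hospitalisation, and modified Fisher is described as grading CV itself, so only values from before randomisation are safe covariates.

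**Conclusion.** The point holds as a matter of efficiency and clarity. The Statistical analyses section fixes no covariate-adjusted analysis of CV, and the steps it does plan do not ensure that modified Fisher, WFNS or Hunt-Hess is used. The cost is about 2 to 13 points of power on a base of about 53%. That rests on 205 evaluable per arm, the 0.1 target read as 60% v 50%, no loss to matching, and an assumed prognostic strength. At the cited 58% v 60% the cost is almost nil. Type I error is not affected. The sample-size discrepancy matters more for power, but it does not remove this defect. The change should be made because it is cheap and also settles which result is the main one.

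**What to change.** In Statistical analyses, name one primary analysis of CV: a logistic regression on randomised arm in all randomised patients, without matching. Fix the covariates as modified Fisher score, WFNS or Hunt-Hess grade (choose one) and age. Use values recorded before randomisation, and include them whether or not the arms differ. Report the adjusted OR with 95% CI and a standardised risk difference. Keep the chi-square test and crude OR as a sensitivity analysis. In Baseline assessment, state that these covariates are recorded before randomisation.

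The cost is a few sentences and one model, with no extra patients and no new variables. The small downside is that the adjusted OR is conditional on the covariates and not on the same scale as the crude OR, which is why the risk difference is reported alongside it.
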